**Questionnaires**									
	Demographics	✓		—^a^		—		—	
	EQ-5D-5L	✓		—		—		✓	
	Self-Care of Heart Failure Index	✓		—		—		✓	
	Kansas City Cardiomyopathy Questionnaire-12	✓		—		—		✓	
	Visual analog scale for dyspnea	✓		—		—		✓	
	Perceptions of Medly program (intervention group only)	—		—		—		✓	
**Health service utilization**									
	Number of hospitalizations in the previous 3 months	✓		—		—		✓	
	Number of days in the hospital in the previous 3 months	✓		—		—		✓	
	Number of emergency department visits in the previous 3 months	✓		—		—		✓	
	Number of clinic visits in the previous 3 months	✓		—		—		✓	
	Number of readmissions to hospital since recruitment	—		—		✓		—	
**Blood test outcomes**									
	N-terminal proBNP^b^/BNP levels	✓		✓		✓		✓	
	Creatinine	✓		✓		✓		✓	
	Sodium	✓		✓		✓		✓	
	Potassium	✓		✓		✓		✓	

^a^Not applicable.

^b^BNP: brain natriuretic peptide.

### Data Collection

Prestudy and poststudy questionnaires will comprise the aforementioned validated survey tools, whereas the poststudy questionnaire for the patients in the intervention group will have additional questions related to their perceptions of Medly. Prestudy and poststudy questionnaires will be administered to both control and intervention groups, which may be completed in the clinic or at home. Participants choosing to complete the questionnaires at home will be provided with prestamped envelopes addressed to the research team. The prestudy questionnaire will be provided to the participants at the time of enrollment, whereas the poststudy questionnaire will be provided after a follow-up appointment with the participant’s clinician at the time of study completion (3 months after enrollment). Data on the 30-day HF readmission rates; HF length of stay; number of visits to the ED; and clinical measures, including creatinine, sodium, potassium, left ventricular ejection fraction, and BNP/NT-proBNP levels, will be determined through the hospital’s electronic medical records and manual chart reviews.

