### Study Protocol

#### Patient Recruitment and Randomization

Patients are recruited within approximately 2 weeks post discharge, often during their regularly scheduled clinician visits for postdischarge care at the participating sites. After clinicians determine if the patient is eligible (inclusion and exclusion criteria can be found in Textboxes 1 and 2, respectively), the patient is asked if they are willing to speak to the study coordinator about enrollment. Informed written consent is obtained from patients by the research coordinator. Each patient is randomized to either the TM intervention or standard care control group. Block randomization is used with random block sizes of 2, 4, or 6 for each site. A Web-based computer-generated randomization tool, Sealed Envelope (Sealed Envelope Ltd.) [23], is used to determine the randomization order. Sequentially numbered envelopes are used to determine if the patient is in the intervention or control arm. The envelopes are prepared by a researcher outside of the study team. The study coordinator and patient are blinded to which group the patient is assigned until the patient has consented to participate in the study. Each participant in the control and intervention group receives a Can $25 Shoppers Drug Mart gift card to compensate them for their time in participating in the study.

Patient inclusion criteria.Adults (18 years or older)Hospitalization duration for decompensated heart failure >24 hoursPatient speaks and reads English adequately to provide informed consent and understand the text prompts in the app (or has an informal caregiver who can translate the prompts for them)Ability to comply with using Medly (eg, able to stand on the weight scale and able to answer symptom questions)

Patient exclusion criteria.Dementia or uncontrolled psychiatric illnessPatients who will require inpatient rehabilitation after dischargeParticipating in another clinical trial that may confound the resultsResidents of long-term care facilitiesTerminal diagnosis of any health condition with a life expectancy of <1 yearUnable to provide informed consentUnable to speak or read English

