#### Intervention Versus Control Groups

Patients in the intervention group will receive standard of care and also Medly, whereas the patients in the control group will receive standard of care. Standard of care will comprise the usual follow-up and routine management performed by each participating institution for patients with HF. Patients in the intervention group will receive the Medly kit to take home after being trained on how to use Medly. The Medly kit includes a mobile phone, with the Medly app, provided to the patient as well as a Bluetooth-enabled weighing scale and blood pressure monitor. Each patient will be followed for 3 months post discharge.

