#### Study Outcome Measures

The primary outcome measures will be self-care as measured through the SCHFI [22] and quality of life as measured through the Kansas City Cardiomyopathy Questionnaire-12 [24] and the EQ-5D-5L [25]. Additional measures will include compliance with Medly utilization determined through the data on the Medly-AID servers regarding the frequency that patients took measurements; shortness of breath as measured using a visual analog scale for dyspnea in the patient questionnaires; and clinical status as measured by the New York Heart Association class, left ventricular ejection fraction, and BNP/N-terminal proBNP (NT-proBNP) levels (obtained via the electronic medical records). Health service utilization will be assessed by 30-day HF readmission rates, HF length of stay, and number of visits to the ED. The cost of the intervention will be determined by tracking the equipment costs and staff resources for clinical, technical, and administrative support and will be compared with the cost of health services. Creatinine, sodium, and potassium levels will also be assessed through routine blood tests from the patients, usually conducted at the participating institution’s laboratories. These values will be obtained through the patients’ electronic medical records. The schedule for data acquisition is depicted in Table 1.

**Table 1 table1:** Schedule for data acquisition indicated by checkmarks at the specified time point.

Data Collected			Baseline		2 weeks		1 month		3 months

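### The baseline questionnaires may be completed at home, so the plan permits baselines of the primary outcomes to be taken after the patient knows the arm

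*Protocol article*

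**What the plan says.** All three primary measures are patient-reported: the Study Outcome Measures section names the SCHFI for self-care, and the KCCQ-12 and EQ-5D-5L for quality of life. Table 1 schedules each of them at baseline and 3 months only.

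On where they are completed, Data Collection states: "Prestudy and poststudy questionnaires will be administered to both control and intervention groups, which may be completed in the clinic or at home". Patients who choose home receive a stamped return envelope and post their answers back. On timing, the section says only that "The prestudy questionnaire will be provided to the participants at the time of enrollment"; it gives no return deadline.

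On knowledge of the arm, Patient Recruitment and Randomization says that coordinator and patient alike stay "blinded to which group the patient is assigned until the patient has consented to participate in the study". On training, the section that describes the two arms states: "Patients in the intervention group will receive the Medly kit to take home after being trained on how to use Medly".

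The Data Analysis section plans between-group t tests or Mann-Whitney tests, and paired tests of baseline against poststudy values within each arm.

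**The concern.** A baseline is useful as a reference because allocation cannot have influenced it. Here the patient may take the prestudy questionnaire home, blinding is guaranteed only up to consent, and no section places completion before the envelope is opened. A patient could therefore answer the baseline questions already knowing the arm. An intervention patient could also do so after training, or after starting to monitor weight, blood pressure and symptoms daily. That monitoring is close to the behavior the SCHFI is used to measure. For the two quality-of-life scales the more general route is that a patient who knows the arm may answer differently.

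With only two scheduled readings per scale, no second pre-treatment value could replace an affected one. A baseline that must be posted back can also be lost, though nothing in the document shows that this would differ by arm.

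**Working it through.** **Order of events.** Read together, the sections fix three things: the arm is concealed until consent, the prestudy questionnaire is handed out at enrollment, and training precedes taking the kit home. They do not fix when the envelope is opened relative to completion of the questionnaire, or whether consent, allocation and training share one visit. Clinic completion before allocation fits the text. So does home completion after allocation and training.

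**Which analyses use the baseline.**
- Within-arm paired tests (planned): affected.
- Comparison of the arms at baseline: affected.
- Between-group test on change scores, or adjusted for baseline: affected.
- Between-group test on 3-month scores alone: not affected.

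**The plan's own figure.** Inputs from Sample Size Calculation: SD 20, difference 10, alpha .05, power 0.8; Data Analysis makes tests 2-tailed. n per arm = 2 × (1.960 + 0.842)² × 20² / 10² = 62.8, so 63, as stated. Power at 63 per arm is Φ(10 / (20 × √(2/63)) − 1.96) = Φ(2.806 − 1.96) = 80.1%. This calculation uses no baseline, so the point does not touch it.

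**Illustrative size.** Let b be the rise in the intervention arm's mean baseline SCHFI, equal to the share completing at home times the mean shift in those patients. Neither factor is in the document. Half at home with a 4-point shift gives b = 0.5 × 4 = 2. A share of 25% to 75% and a shift of 2 to 6 points give b from 0.25 × 2 = 0.5 to 0.75 × 6 = 4.5.

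Assume that the true 3-month difference is 10, both time points have SD 20, their correlation is r, and the shift alters only the mean. Then:
- change score: effect 10 − b, SD 20√(2(1 − r));
- ANCOVA: effect 10 − r·b, residual SD 20√(1 − r²).

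For r = 0.5 and b = 2:
- change score: effect 8, SD 20, power Φ(8/3.563 − 1.96) = Φ(0.285) = 61.2%;
- ANCOVA: effect 9, SD 17.32, power Φ(9/3.086 − 1.96) = Φ(0.956) = 83.1%.

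Power at 63 per arm over a range of assumptions:

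| r | Analysis | b = 0 | b = 1 | b = 2 | b = 3 | b = 5 |
|---|---|---|---|---|---|---|
| 0.3 | change | 66.0% | 56.9% | 47.5% | 38.2% | 21.9% |
| 0.3 | ANCOVA | 83.7% | 81.4% | 79.0% | 76.3% | 70.6% |
| 0.5 | change | 80.1% | 71.4% | 61.2% | 50.2% | 28.9% |
| 0.5 | ANCOVA | 90.0% | 86.8% | 83.1% | 78.7% | 68.1% |
| 0.7 | change | 95.2% | 90.3% | 82.6% | 71.8% | 44.1% |
| 0.7 | ANCOVA | 97.6% | 95.5% | 92.2% | 87.4% | 72.4% |

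A test of 3-month scores alone stays at 80.1% in every column.

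**The case against.** The strongest reply has three parts.

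First, the order of steps at an enrollment visit is a detail that a journal article may leave to the full protocol, and nothing in the article shows that any baseline was completed late. This stands as far as the sequence goes. It does not remove the point, because home completion of the prestudy questionnaire is something the article expressly allows, not something it leaves out.

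Second, the article names neither ANCOVA nor a change-score contrast, and the sample size rests on a plain two-group difference. If the between-group test uses 3-month scores, the randomized comparison is untouched, and a baseline never returned would not remove a patient from it. This also stands. The within-arm paired tests are the only tests in the article that certainly use the baseline, and they do not estimate the randomized effect.

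Third, the home share, the shift and the correlation are all assumed. With ANCOVA at r = 0.5, a 2-point shift still leaves power above the planned 80%. This is correct, and it is why the figures serve as illustration only.

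A reader might go further and infer that every home baseline is a post-randomization measure, that the treatment effect estimate is therefore biased, or that power is really about 60%. The document supports none of these. The first needs a visit sequence it does not state, the second an analysis it does not specify, and the third a change score with SD 20 (r = 0.5) and a 2-point shift.

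**Conclusion.** The point holds as a permission in the plan that should be closed. As written, baselines of the patient-reported primary outcomes may be completed after the arm is known and possibly after Medly training. Where that happens, the paired tests, the baseline comparison and any change-score or baseline-adjusted contrast would be distorted; a comparison of 3-month scores alone would not.

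Size and direction are unknown. If training raises early SCHFI answers, a change-score contrast shrinks; if it makes patients judge their self-care more critically, the contrast grows. A 2-point rise is one fifth of the 10-point planning difference. Under the assumptions shown with r = 0.5, it costs about 19 percentage points of change-score power (80.1 − 61.2) or about 7 points of ANCOVA power (90.0 − 83.1). The stated sample size is unaffected. The change is recommended; the document does not show that the primary comparison is invalid without it.

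**What to change.** State that the prestudy questionnaire is completed and collected in the clinic, after consent and before the randomization envelope is opened, and that the date and time of completion are recorded. Keep the home and mail option for the poststudy questionnaire only.

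For participants already enrolled (35 by July 30, 2019), flag any baseline dated after randomization and run a sensitivity analysis without those baselines for every analysis that uses them. At that date 144 − 35 = 109 baselines were still to come and could be protected.

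The cost is a few extra minutes at the enrollment visit, where the coordinator is already present to obtain consent. No endpoint or sample size changes.

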#### Semistructured Interviews

Using purposive sampling, semistructured interviews at the end of the study will also be conducted with a subset of patients in the intervention group to receive feedback from patients with different experiences using Medly-AID. Participants for the interviews will be selected based on varying adherence to taking measurements, number of readmissions to hospital, difficulties in using Medly, etc. Interviews will be conducted until data saturation is reached (ie, interviewer determines no new relevant information is being collected), which is typically 15 to 20 participants. The interviews are expected to last for 20 min to 30 min and will be conducted in a quiet and private space within the clinic (eg, consultation room) during a regular clinic visit or over the telephone. All interviews will be audiotaped and transcribed for later analysis. Clinicians providing care for patients using Medly-AID will also undergo a semistructured interview post study to determine their perceptions of the use and impact of Medly-AID. It is anticipated that the clinician interviews will last for 15 min to 45 min.

#### Data Analysis

For each outcome measure, normality of the data will be verified using the Kolmogorov-Smirnov and Shapiro-Wilk tests of normality. Between-group analyses using independent Student *t* tests and Mann-Whitney tests (for normally and nonnormally distributed data, respectively) will be performed. Paired Student *t* tests and Wilcoxon signed rank tests will also be performed to compare baseline and poststudy data for both the intervention and control groups as appropriate. The statistical analyses will be performed using the statistical software SPSS 17.0 (IBM Corporation). Statistical significance will be considered at *P*<.05, unless otherwise specified. All reported test results will be 2-tailed.

The transcribed interview data will be analyzed using conventional content analysis, whereby 2 researchers will analyze the transcripts for themes independently [26]. The 2 researchers will then discuss the themes and issues that emerge until a consensus is reached. Triangulation, which is validation of the findings through the collection of data from different sources or methods, will be used for this study. Specifically, the interview findings will be used to try to confirm and explain the results of the quantitative data, including health services utilization and Medly usage.

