### Sample Size Calculation

A sample size calculation was based on the Self-Care of Heart Failure Index (SCHFI), using a population standard deviation of 20 and an effect size of 10 as determined in previous studies (alpha=.05; power=0.8) [22]. The required sample size was calculated to be 63 per group. To compensate for patients who will be lost to follow-up during the course of the study, 72 patients will be recruited for the intervention group and 72 patients for the control group.

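### Normality tests choose the between-arm analysis, so the primary effect measure is not fixed in advance, and no baseline or site adjustment is named although both are available

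*Protocol article*

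**What the plan says.** The Data Analysis section sets one rule for every outcome measure. First, "normality of the data will be verified using the Kolmogorov-Smirnov and Shapiro-Wilk tests of normality". Then the arms are compared: "Between-group analyses using independent Student *t* tests and Mann-Whitney tests (for normally and nonnormally distributed data, respectively) will be performed". No covariate and no site term is named. The only stated use of the baseline scores is in paired tests within each arm, which do not compare the arms. The section does not say whether the between-arm test is applied to 3-month scores or to change from baseline.

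Elsewhere the article provides what an adjusted analysis needs. Table 1 schedules the "Self-Care of Heart Failure Index" (SCHFI), KCCQ-12, EQ-5D-5L and the dyspnea scale at baseline and 3 months, and the Data Collection section gives the questionnaires to both arms. Under Patient Recruitment and Randomization, "Block randomization is used with random block sizes of 2, 4, or 6 for each site". The Sample Size Calculation rests on a mean difference in SCHFI points, "using a population standard deviation of 20 and an effect size of 10 as determined in previous studies".

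**The concern.** There are two separate issues.

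**The effect measure depends on the data.** The trial is sized to detect a difference of 10 points. If a normality test rejects, the between-arm comparison becomes a Mann-Whitney test, which does not estimate a difference in means. The three primary questionnaires could be analysed by different methods, and which method applies to which would be known only after the data are in.

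**Available precision is not used.** A baseline score that correlates with the 3-month score explains part of the outcome variance. Leaving it out of the between-arm comparison keeps that variance in the error term. The same holds, on a smaller scale, for site, which the randomization already balances. The article itself lists the relatively small sample as a limitation (Strengths and Limitations of the Study), so unused precision matters here.

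**Working it through.** **Inputs from the article.** SCHFI difference 10, SD 20 (standardized difference 0.5); "alpha=.05; power=0.8"; "All reported test results will be 2-tailed"; "The required sample size was calculated to be 63 per group", raised to 72 per group for losses.

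**Inputs not in the article (assumed).** The correlation r between baseline and 3-month score, taken as 0.1 to 0.7; the share f of outcome variance explained by site, taken as 2% to 10%.

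**Step 1: the plan's own figure.** n per arm = 2 × (1.960 + 0.842)² × 20² / 10² = 62.8, so 63. This reproduces. The t-based calculation gives 63.8, so 64. Power at 63 per arm is 80.1% by the normal approximation and 79.5% by the t distribution. The figure of 72 corresponds to 12.5% loss: 63 / (1 − 0.125) = 72.

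**Step 2: three ways to compare the arms at 63 per arm.** All powers are t-based and two-sided at 0.05.
- Unadjusted 3-month scores: d = 10/20 = 0.5.
- Change scores: SD = 20 × √(2(1 − r)), so d = 0.5 / √(2(1 − r)).
- ANCOVA on baseline: residual SD = 20 × √(1 − r²), so d = 0.5 / √(1 − r²).

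| Assumed r | 3-month score | Change score | ANCOVA | Unadjusted n per arm matching ANCOVA, 63/(1 − r²) |
|---|---|---|---|---|
| 0.1 | 79.5% | 55% | 80% | 64 |
| 0.3 | 79.5% | 65% | 83% | 69 |
| 0.5 | 79.5% | 80% | 90% | 84 |
| 0.7 | 79.5% | 95% | 97% | 124 |

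Example at r = 0.5: the ANCOVA residual SD is 20 × √0.75 = 17.32, d = 0.577 and power is 89.5%. The change-score SD is 20 × √1 = 20, so its power equals that of the 3-month score. Below r = 0.5 the change score does worse than the unadjusted 3-month score. ANCOVA is ahead of both in every row.

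**Step 3: site alone.** With residual SD = 20 × √(1 − f), power is 80.3%, 81.5% and 83.5% for f = 2%, 5% and 10%, against 79.5% with no adjustment.

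**Step 4: simulation check.** 4,000 runs per setting, 63 per arm, 3 sites, r = 0.3 to 0.7. With a true difference of 10, the unadjusted t test rejected in 79% to 81% of runs, and the model with baseline and site in 83% to 98%. With no true difference and site explaining 5% of variance, the unadjusted test rejected in 4.2% to 4.6% of runs and the adjusted model in about 5%. Omitting site therefore makes the test slightly conservative.

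**The case against.** The strongest reply is that design and analysis agree. The trial is sized for an unadjusted comparison with SD 20, and an unadjusted t test delivers essentially the stated power. In a randomized trial that test is valid. All of this stands. A reader might infer from the missing covariates that the trial is underpowered or that its test is invalid; the documents support neither.

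A reader might also infer that the between-arm comparison ignores the baseline scores altogether. The text does not establish this, because a comparison of changes would use them. What can be said is that neither reading matches ANCOVA.

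The size of the gain rests on a correlation that the article does not give. Baseline is taken within about two weeks of discharge after decompensation, so a low correlation is possible. At r = 0.1 the gain over the 3-month score is only 0.4 points (79.9% against 79.5%), and at r = 0.3 it is under 4 points. The figures at r = 0.7 should not be quoted alone. The power gain from site is small and does not carry the point.

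Baseline questionnaires may be completed at home and mailed, so some may be missing. A complete-case ANCOVA would drop those patients: at r = 0.3, losing 6 per arm (57 left) gives 79.2% power, which cancels the gain. This is a sound warning against complete-case analysis. It does not defeat adjustment, because missing baselines can be filled in without losing patients. Some baselines may also be completed after the arm is known. That caution remains, and it applies equally to change scores.

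A mean difference could still be reported beside a Mann-Whitney P value, since the article does not exclude it; but the stated test would not be a test of that difference. What to do if the two normality tests disagree may be settled in an analysis plan that is not shown, and nothing here depends on it. The choice of test by normality testing is different: the article states it as the method.

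**Conclusion.** The point holds as a matter of prespecification and efficiency. The article fixes a rule under which normality tests decide, outcome by outcome, between a t test and a Mann-Whitney test. The primary effect measure is thus not settled in advance and may not be the mean difference used for sizing. No cost of this rule in type I error or power was calculated; the objection is to the unsettled effect measure.

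Relative to unadjusted 3-month scores, baseline adjustment at 63 per arm would raise power from 79.5% to between 80% and 97% over the assumed r of 0.1 to 0.7. Relative to change scores, the gain runs from about 25 points at r = 0.1 (80% against 55%) to about 2 points at r = 0.7. Site adjustment alone gives about 80% to 84% if site explains 2% to 10% of variance; its main merits are that it matches the randomization and removes a slight conservatism. These figures assume SD 20, a true difference of 10 and 63 evaluable patients per arm. The plan is not invalid or underpowered on its own assumptions; it leaves a free improvement unused.

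**What to change.** For SCHFI, KCCQ-12, EQ-5D-5L and dyspnea, prespecify one linear model of the 3-month score on arm, baseline score and site. Report the adjusted mean difference with its 95% CI as the between-arm result. This also settles whether 3-month scores or changes are analysed.

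Remove the normality tests as the means of choosing the analysis. Use robust or bootstrap standard errors to guard against non-normal residuals, and keep rank tests as sensitivity analyses only.

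Handle missing baseline scores by simple imputation, for example the overall mean or a missing indicator, so that no randomized patient with a 3-month score is dropped.

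The cost is a change of wording in the protocol or analysis plan. No further data or patients are needed. At the time of the article recruitment was under way and final analysis was expected in fall 2020, so the change could be made before that analysis.

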### Objectives

The main objective of the *Medly-After an Incidence of acute Decompensation* (Medly-AID) trial is to determine the effect of Medly on the self-care and quality of life (primary outcome measures) of patients with HF who have been recently discharged from hospital after a HF-related acute decompensation. Acute decompensation is when there is a sudden worsening of signs and symptoms of HF, which often leads to a visit to the emergency department (ED) or hospitalization. Secondary outcome measures include the cost of health care services used and health outcomes. A main difference between the Medly-AID trial and the previous Medly RCT is that the Medly-AID trial will be restricted to patients who have been discharged from hospital during the 2 weeks before recruitment, thus targeting the patients at the highest risk for rehospitalization.

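### Within-arm baseline-to-3-month tests are planned at P<.05 with no descriptive label, although eligibility builds a fall into the hospitalization and hospital-day counts and one-arm significance is no evidence for Medly

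*Protocol article*

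**What the plan says.** The Data Analysis section first plans the randomized comparison: "Between-group analyses using independent Student *t* tests and Mann-Whitney tests (for normally and nonnormally distributed data, respectively) will be performed". It then adds that "Paired Student *t* tests and Wilcoxon signed rank tests will also be performed to compare baseline and poststudy data", for the intervention and the control group alike, as appropriate. One threshold covers everything: "Statistical significance will be considered at *P*<.05, unless otherwise specified", and "All reported test results will be 2-tailed". Nothing labels the paired tests descriptive or ranks them below the between-group tests.

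Three other places decide what these tests would measure:

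- The Objectives say the trial is "restricted to patients who have been discharged from hospital during the 2 weeks before recruitment".
- The inclusion criteria require a stay of more than 24 hours for decompensated heart failure.
- Table 1, under health service utilization, lists "Number of hospitalizations in the previous 3 months", together with hospital days over the same look-back. Both are collected at baseline and at 3 months.

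**The concern.** A within-arm change from baseline mixes any Medly effect with whatever else happens between the two visits. In this trial two such influences matter.

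First, patients are selected because they were recently in hospital. The index discharge lies at most about two weeks before recruitment, well inside the three-month look-back. Unless the data form excludes the index stay, the baseline hospitalization count is at least 1 for every patient, and hospital days exceed one. The 3-month values can be zero. A fall is then largely a product of eligibility.

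Second, quality of life, dyspnea and natriuretic peptides are first measured soon after a decompensation. Some recovery without Medly is plausible, though its size is not given. If it is moderate, each arm may or may not cross .05 by chance, and significance with Medly but not in control is easily read as a treatment effect.

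What is at stake is interpretation. The Strengths and Limitations section expects the trial to be underpowered for readmission rates. A null between-arm result on utilization could therefore stand next to a highly significant fall in the Medly arm.

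**Working it through.** **1. The plan's own figure.** Inputs from Sample Size Calculation: SD 20, difference 10, two-sided alpha .05, power 0.80.

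n per arm = 2 × (1.960 + 0.842)² × 20² / 10² = 62.8, so 63. This reproduces the stated figure. With 12.5% loss, 63 / 0.875 = 72, which also agrees. I use 63 evaluable patients per arm.

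**2. Follow-up rate for hospitalizations.** The only rate in the document is in the Background: about 20% readmitted within 30 days. As a Poisson mean this is −ln(0.8) = 0.22 per 30 days.

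- No further admissions after day 30: mean 0.22 over 3 months.
- Constant hazard for 3 months: 3 × 0.22 = 0.67.

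The Background says the risk is highest in the first weeks, so 0.67 is towards the high end of what the 20% figure implies. A higher follow-up mean makes a significant fall less likely.

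**3. Simulation with no Medly effect.** The same distribution is used in both arms: baseline exactly 1 (index stay only), 3-month count Poisson, 63 per arm, Wilcoxon signed rank test in each arm at two-sided .05, counting only falls. There were 6,000 runs per row.

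| Follow-up mean | Significant fall in a given arm | Significant fall in both arms |
|---|---|---|
| 0.22 | 100% | 100% |
| 0.4 | >99.9% | >99.9% |
| 0.5 | 99.9% | 99.6% |
| 0.67 | 86% | 76% |
| 0.8 | 48% | 23% |
| 1.0 | 5% | 0.2% |

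Allowing 0.25 earlier admissions per patient on average (baseline mean 1.25) raises the both-arms figure at 0.67 to about 99%. Overdispersed follow-up counts at 0.67 (gamma mixing, shape 1, assumed) give 67%. Hospital days carry the same built-in excess but were not simulated.

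**4. Questionnaires.** SD 20 at both visits is taken from the sample size section. The pre-post correlation r and the natural recovery d, equal in both arms, are assumptions.

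SD of change = 20 × √(2(1 − r)), which is 20 at r = 0.5. Its standard error is 20/√63 = 2.52. Let p be the noncentral-t power of the paired test (62 df) for a significant improvement in one arm. Then P(both arms) = p² and P(Medly only) = p(1 − p).

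| Recovery d, r = 0.5 | p | Both arms | Medly only |
|---|---|---|---|
| 0 | 0.025 | 0.1% | 2.4% |
| 3 | 0.215 | 4.6% | 17% |
| 5 | 0.497 | 25% | 25% |
| 7 | 0.781 | 61% | 17% |
| 10 | 0.974 | 95% | 2.5% |

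At d = 5, r = 0.3 to 0.7 gives Medly only in 24% to 21% of trials and both arms in 14% to 51%. By symmetry, at d = 5 and r = 0.5, exactly one arm is significant in 2 × 25% = 50% of trials.

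**The case against.** The strongest reply is that the randomized comparison is planned and comes first, that the paired tests are additional, and that no sentence says they will support an efficacy claim. That is correct. A reader might infer that the plan discards the randomized comparison; the text does not support this.

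Nor does it support the reading that all outcomes must improve and that both arms will therefore show significance. The document gives no natural course for the SCHFI, KCCQ-12, EQ-5D-5L, dyspnea or natriuretic peptides. The SCHFI, on which the trial is sized, measures self-care and need not change in controls. The second table shows how far the answer depends on the assumed recovery.

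It is also fair that Data Analysis does not name the hospitalization count as a paired outcome. Its use there is inferred from the reference to baseline and poststudy data together with Table 1, and the qualifier about appropriateness could exclude it. That qualifier can equally mean the choice between t test and Wilcoxon, and the section opens by addressing every outcome measure.

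Finally, if both arms fall, the control arm itself shows that the fall is not due to Medly. This stands for a reader who sees both arms. It does not help when only one arm is significant, or when the Medly result is quoted alone.

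A condensed article may leave much to an analysis plan. Here, however, it states the tests and their threshold, and that choice can be assessed as written.

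**Conclusion.** The point holds in limited form. The planned paired tests yield P values that cannot separate a Medly effect from selection or natural recovery.

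For the hospitalization count the artefact is large: at rates derived from the document's own 20% figure, 76% to 100% of null trials show a significant fall in both arms. This rests on Poisson counts, equal rates in the arms, a baseline that includes the index stay, and that count being tested in paired form. It weakens quickly above a follow-up mean of 0.67 and is gone near 1.0 when the baseline is exactly 1.

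For the questionnaires no general statement is possible. Under moderate assumed recovery, Medly-only significance arises by chance in up to about a quarter of trials, so it is not evidence of benefit. The between-group analysis itself is not affected. The change should be made because it costs almost nothing and removes a foreseeable misreading.

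**What to change.** Three changes are enough:

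1. In Data Analysis, replace the paired tests by within-arm mean changes with confidence intervals, labelled descriptive and without P values.
2. State that every conclusion about the effect of Medly rests on the between-arm comparison.
3. Record the index admission (stay and days) separately on the baseline form, and leave it out of any pre-post comparison of utilization counts.

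The cost is a few sentences, one data-form instruction and the loss of the within-arm P values. Within-arm summaries need not be deleted, and no count model with a covariate is required.
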